### Feasibility and acceptability of research processes including recruitment and data collection

#### Rate of research recruitment

Determined by the number of individuals who consent to research divided by the total number of individuals invited to participate in research divided by the number of days in the recruitment period.

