### Recruitment

Patients will be referred to the WNP by PCPs. All patients scheduled for a WNP appointment will be eligible for participation in a single-arm, 12-month pilot study. We anticipate that the Weight Navigator will see approximately 4 patients per 4-h clinic session once per week. Accounting for vacations, holidays, and canceled appointments, we estimate that the Weight Navigator will see approximately 150 patients during the first year of the program.

All patients scheduled for a WNP appointment will be eligible for participation in a single-arm, 12-month pilot research study. A research project manager will contact scheduled patients by telephone at least 5 days prior to their appointment date to invite them to participate in research and describe the study processes. Individuals who desire to participate in research will complete an online informed consent document and the baseline survey prior to the WNP appointment using the RedCap survey platform (REDCap, n.d.). Recruitment will continue until we reach our target of 30 participants.

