### Outcome measures

We have 4 outcome categories: (1) feasibility and acceptability of the WNP; (2) clinical impact of the WNP; (3) feasibility, acceptability, and preliminary effectiveness of adding remote weight monitoring by text messaging to the WNP; and (4) feasibility and acceptability of research processes including recruitment and data collection.

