### Future directions

We plan to evaluate the pilot WNP using mixed quantitative and qualitative data collection methods. These data will enable us to evaluate the program’s feasibility, acceptability, and preliminary weight loss effectiveness. Moreover, we will use qualitative data obtained during interviews with patients to identify the features of the program that work well and those that could be improved. These data will enable us to refine the program and test its effectiveness in diverse practice settings. We anticipate evaluating the refined program in a future large-scale pragmatic trial using an effectiveness-implementation hybrid type 1 design to evaluate the program’s weight loss effectiveness at 12 and 24 months while also gathering information on implementation processes and determinants (Curran *et al.*, 2012).

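### The recruitment rate divides the consent proportion by days, so one number merges acceptance and pace and shows neither

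*Protocol article*

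**What the plan says.** Under Outcome measures, the Protocol article lists four outcome categories. The fourth is "feasibility and acceptability of research processes including recruitment and data collection". Within it, the section Rate of research recruitment gives a complete operational definition: the number who consent, "divided by the total number of individuals invited to participate in research divided by the number of days in the recruitment period". The consent count is thus divided twice in succession, first by the number invited and then by the number of days.

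The Recruitment section fixes the numerator at completion: "Recruitment will continue until we reach our target of 30 participants". It also describes the supply of people to invite. The Weight Navigator is expected to see "approximately 4 patients per 4-h clinic session once per week", and "we estimate that the Weight Navigator will see approximately 150 patients during the first year of the program". Invitations are tied to the appointment schedule: "A research project manager will contact scheduled patients by telephone at least 5 days prior to their appointment date to invite them".

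The article defines no separate consent proportion (consented ÷ invited) and no separate accrual rate (consented ÷ time). It gives no expected number invited and no expected recruitment period.

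**The concern.** A pilot usually needs two facts about recruitment: what share of those approached agree, and how many join per unit of time. The first tells a later team how many people to approach. The second tells them how long recruitment will take or how many sites they need. Dividing the first quantity by the number of days yields a proportion per day, which answers neither question. Two pilots that differ in both acceptance and pace can report the same figure, and one pilot's figure changes if it simply aims for a different number of participants.

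This is a stated rule, not a detail left to a fuller document. If the team follows it literally, the reported outcome cannot be interpreted on its own.

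**Working it through.** **Notation and inputs**
- C = number consenting. C = 30 at the end of recruitment (Recruitment section).
- I = number invited and D = days of recruitment. Neither is given, so the values below are assumptions.
- Clinic flow: about 4 patients per week at capacity, and about 150 in year one, or 150/52 = 2.9 per week (Recruitment section). I use these as a guide to plausible invitations per week.
- The article states no recruitment-rate figure, so there is none to reproduce.

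**Step 1. The definition as written**

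Rate = (C/I)/D. With C = 30, Rate = 30/(I × D). Only the product I × D matters.

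**Step 2. Two cases within stated capacity, both with I × D = 6,000**

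| Invited | Days | Invitations per week | Consent (C/I) | Accrual per 30 days | Defined rate |
|---|---|---|---|---|---|
| 50 | 120 | 50/120 × 7 = 2.9 | 60% | 30/120 × 30 = 7.5 | 0.60/120 = 0.005 |
| 40 | 150 | 40/150 × 7 = 1.9 | 75% | 30/150 × 30 = 6.0 | 0.75/150 = 0.005 |

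The first case has the faster pace and the second has the better acceptance. The defined rate cannot tell them apart.

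**Step 3. How wide the overlap can be while staying at or below about 4 invitations per week (I × D about 8,760)**

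| Invited | Days | Invitations per week | Consent | Accrual per 30 days | Defined rate |
|---|---|---|---|---|---|
| 40 | 219 | 1.3 | 75% | 4.1 | 0.0034 |
| 60 | 146 | 2.9 | 50% | 6.2 | 0.0034 |
| 70 | 125 | 3.9 | 43% | 7.2 | 0.0034 |

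So consent from 43% to 75% and accrual from 4.1 to 7.2 per 30 days can share one value.

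**Step 4. Dependence on the target**

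Suppose invitations arrive at r per day and a proportion p accept. Reaching a target of N takes D = N/(p × r) days, so Rate = p/D = p² × r/N. With p = 0.5 and r = 150/365 = 0.411:
- N = 30: 0.25 × 0.411/30 = 0.0034
- N = 60: 0.25 × 0.411/60 = 0.0017

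Acceptance and pace are the same in both lines. Only the target changed, and the value halved.

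**Step 5. The other reading of the chained division**

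Read as C/(I/D) = C × D/I, the two cases in Step 2 give 30 × 120/50 = 72 and 30 × 150/40 = 112.5. For a given acceptance this figure rises as recruitment takes longer, so it is not a recruitment rate either.

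**The case against.** The strongest reply is that invitations and days are not free to vary independently. Patients are invited only after being scheduled with one clinician, so invitations should roughly follow clinic flow. If flow is held at 150 per year, the formula does separate good recruitment from poor. By p² × r/30, consent of 75%, 50% and 25% gives 0.0077, 0.0034 and 0.0009. That stands: the overlap in Steps 2 and 3 requires flow to differ, for instance because referrals start slowly or not every scheduled patient is reached. It also means that contrasts needing far more than 4 invitations per week, or full consent at a trickle of invitations, should not be pressed. It does not rescue the measure. Even at constant flow the value squares the acceptance, so a threefold difference in consent (75% against 25%) appears as a ninefold difference in the rate (0.0077/0.00086 = 9), and the value still depends on the target.

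A second reply is that computing the formula requires all three counts, so nothing is lost in data collection. That also stands. The article does not commit to reporting the counts, but nor does it say they will be withheld.

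A reader might also infer that the formula perversely rewards inviting fewer people. It does not: with 30 consents fixed, needing fewer invitations means higher acceptance, which is a real success. Likewise, with the number fixed, a longer period means slower accrual, and a measure of pace ought to fall. The fault is that the two dimensions are merged, not that either points the wrong way.

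**Conclusion.** The point holds. As defined, the recruitment rate is a proportion per day that reveals neither acceptance nor pace. Different experiences compatible with the stated clinic capacity give the same value: 60% consent at 7.5 per 30 days and 75% at 6.0 per 30 days both score 0.005. This rests on the written definition, the stopping target of 30 and elementary algebra. The particular numbers invited and days are assumptions, and so is the use of patients seen as a guide to patients invited.

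Two stronger conclusions are not supported. A reader might infer that the pilot will be unable to inform recruitment in a later study. That is true only of the single number taken alone, because both useful measures can be recovered if the counts are reported. A reader might also infer that planning of the later trial rests on this rate. Under Future directions the article says "We anticipate evaluating the refined program in a future large-scale pragmatic trial", but it ties no sample size, threshold or go/no-go decision to the recruitment rate. The measure sits in the fourth outcome category. The weight outcomes and the program's own feasibility measures are unaffected. This is a flaw in an outcome definition that should be corrected, not a threat to the study.

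**What to change.** Replace the single definition with two:
- **Consent proportion** = number consenting ÷ number invited.
- **Accrual rate** = number consenting ÷ months (or weeks) of recruitment.

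Report the three counts (consented, invited, length of the recruitment period) beside them. For the two cases in Step 2 this would show 60% with 7.5 per 30 days, against 75% with 6.0 per 30 days, and the difference would be visible at once.

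The cost is one or two lines of wording. The data are those the present formula already requires, with no added burden on participants or staff.

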#### Research retention

Determined by the number of research participants who complete surveys at 6 and 12 months divided by the total number of research participants.

### Data analyses

#### Quantitative data analysis

Measures of central tendency (eg, proportions, means, standard deviations) will be used for all descriptive analyses. We will calculate mean 3-month and 6-month weight changes from baseline. We will also calculate the number of participants that achieve ≥5% body weight loss at 6 and 12 months. We will compare between-group changes (ie, all WNP participants versus WNP research participants and all WNP participants versus matched cohort) in weight using a difference-in-difference analytic approach. Among WNP research participants, we will also calculate mean weight change based on MPOTA-WM data. We will conduct all analyses using Stata 15.

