**Methods::**

Quality improvement program with an embedded, 12-month, single-arm pilot study. Patients with obesity and ≥1 weight-related co-morbidity may be referred to the WNP by PCPs. All patients seen within the WNP during the first 12 months of clinical operations will be compared to a matched cohort of patients from another primary care site. We will recruit a subset of WNP patients (*n* = 30) to participate in a remote weight monitoring pilot program, which will include surveys at 0, 6, and 12 months, qualitative interviews at 0 and 6 months, and use of an electronic health record (EHR)-based text messaging program for remote weight monitoring.

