#### Clinical impact of the WNP

##### Change in weight

We will abstract weight and height data from the EHR for all WNP patients who complete a clinic visit within the first 12 months of clinical program operations. We will evaluate average weight change among WNP patients during the 12 months following their WNP appointment. We will also identify a contemporaneous cohort of patients with obesity matched by gender and approximate age (within 10 years) to WNP patients. The matched cohort will be selected from another Michigan Medicine primary care clinic located less than 1 mile from the pilot site clinic and serving a similar patient population. We will compare between-group weight change among WNP patients and the matched cohort. In addition to evaluating mean weight change, we will also evaluate achievement of ≥5% body weight loss.

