## Discussion

We describe the design, rationale, and study protocol for a quality improvement initiative with an embedded single-arm pilot study. The WNP aims to overcome the known challenges of providing evidence-based obesity management in general practice settings. This model consists of three components that have demonstrated effectiveness when used independently for other primary care improvement efforts: (1) team-based collaborative care; (2) personalized weight management plans; and (3) population health management to optimize patients’ outcomes.

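### The planned contrast of all WNP participants with WNP research participants compares a group with its own subset and so shrinks the difference by about a fifth

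*Protocol article*

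**What the plan says.** The Quantitative data analysis section plans to compare between-group changes "in weight using a difference-in-difference analytic approach" and names two pairs of groups: "ie, all WNP participants versus WNP research participants and all WNP participants versus matched cohort".

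Other sections define these groups:
- **Research participants.** The Abstract (Methods) says "We will recruit a subset of WNP patients", with n = 30. Recruitment says "All patients scheduled for a WNP appointment will be eligible for participation in a single-arm, 12-month pilot research study" and "Recruitment will continue until we reach our target of 30 participants".
- **All WNP participants.** Under Clinical impact of the WNP, Change in weight, EHR weights are taken "for all WNP patients who complete a clinic visit within the first 12 months of clinical program operations". Research participants are not excluded. On numbers, Recruitment says "we estimate that the Weight Navigator will see approximately 150 patients during the first year of the program".

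The Intervention section offers text-message weight reporting, with the outreach it triggers, to research participants only. Outcome measures lists early evidence that remote monitoring adds to the WNP as part of its third outcome category.

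**The concern.** A comparison meant to show what remote monitoring adds needs patients who had it on one side and patients who did not on the other. As written, the comparator is everyone seen in the program, including the patients who were monitored. Any difference between monitored and unmonitored patients is partly cancelled by the monitored patients' own presence in the comparator.

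This is the only planned between-group contrast that bears on the added value of monitoring. The other weight analysis for monitoring is a change from baseline within the MPOTA-WM users, which has no comparator. Future directions says that the pilot results will be used to refine the program before a larger trial, so an understated difference could carry into that planning. A second problem follows if the overlapping groups are put through a two-sample analysis that treats them as independent, because the variance is then wrong.

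**Working it through.** The article gives no effect size, SD, alpha or power for this contrast, so there is no stated figure to reproduce.

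**Inputs from the article:** research group n = 30; all WNP patients N about 150; the 30 are nested in the N.

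**Assumptions made here:** a common SD of weight change in both groups; two-sided 5% test; normal approximation; all 30 research participants complete a WNP visit. N is varied because 150 is itself an estimate: 120 as a low value, 180 as an intermediate one, and 208 as the ceiling of 4 patients × 52 weekly sessions.

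**Step 1: size of the estimate.** The all-WNP mean is a weighted average of the research mean (weight n/N) and the non-research mean (weight 1 − n/N). Hence

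mean(research) − mean(all) = (1 − n/N) × [mean(research) − mean(non-research)].

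With 30 of 150 the factor is 1 − 0.20 = 0.80. This is an identity and needs no assumption about SD, test or model.

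**Step 2: standard error, in SD units.**
- Groups treated as independent: √(1/150 + 1/30) = √0.0400 = 0.200.
- Correct for the nested difference: 0.80 × √(1/120 + 1/30) = 0.80 × 0.204 = 0.163.
- Ratio: 0.200 / 0.163 = 1.22, so the independent-groups SE is about 22% too large.

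**Step 3: actual type I error under the independent-groups SE.** 2Φ(−1.96 × 1.2247) = 0.016. A simulation of 100,000 data sets with no true difference gave 0.015.

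**Step 4: power at an assumed true research versus non-research difference of 0.5 SD.**
- Nested, independent-groups SE: Φ[(0.80 × 0.5 − 1.96 × 0.200) / 0.163] = Φ(0.05) = 0.52.
- Disjoint, 30 versus 120: Φ(0.5 / 0.204 − 1.96) = Φ(0.49) = 0.69.
- Nested, correct SE: (0.80 × 0.5) / (0.80 × 0.204) = 0.5 / 0.204. The factor 0.80 cancels, the z-statistic equals the disjoint one, and power is again 0.69.

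| N | Factor on the estimate | Independent-groups SE too large by | Actual type I error | Power at 0.5 SD, nested with independent-groups SE | Power at 0.5 SD, disjoint |
|---|---|---|---|---|---|
| 120 | 0.75 | 29% | 0.011 | 0.44 | 0.66 |
| 150 | 0.80 | 22% | 0.016 | 0.52 | 0.69 |
| 180 | 0.83 | 18% | 0.020 | 0.57 | 0.71 |
| 208 | 0.86 | 16% | 0.023 | 0.61 | 0.72 |

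The third to fifth columns apply only if the overlap is ignored in the variance. The second applies whenever the groups are taken as written.

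**The case against.** The strongest reply is that the article names a difference-in-difference approach but no model, variance formula or test. An analyst who codes one research indicator within a single WNP data set gives each patient one code, and the comparison becomes disjoint. If the 30 patients' records were instead duplicated and clustered by patient, the variance would no longer be the independent-groups one. This stands as far as the standard error goes. A reader might infer that the stated comparison by itself produces wrong standard errors and loses 17 points of power. It does not: step 4 shows that the loss disappears once the variance allows for the overlap. The reply does not dispose of the estimate. The article fixes the groups, and clustering would leave the factor of 0.80 in place. A disjoint coding would remove it, but that is a different comparison from the one written.

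A second reply is that the article never assigns this contrast to the monitoring question; it could be a check on how representative the research subset is. That is possible. But the article lists the preliminary effectiveness of monitoring as an outcome and offers no other between-group analysis that touches it.

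A reader might also extend the criticism to the matched-cohort contrast, since the Discussion says "This model consists of three components" and only about 30 of 150 WNP patients would receive the monitoring component. The documents do not support calling that an error. The matched patients come from another clinic, so no patient is on both sides. The article sets all WNP patients against the matched cohort consistently, which is a legitimate estimate of the program as delivered, and it lists monitoring as a separate outcome category.

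Finally, separating the groups does not isolate a monitoring effect. Research participants must be willing to complete surveys, text their weight and accept outreach, so they may differ in motivation from those who decline. This stands, and the bias cannot be sized from the article.

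**Conclusion.** The point holds for the first contrast. As written, it estimates 0.80 of the research versus non-research difference at the article's own figures of 30 and about 150, and 0.75 to 0.86 for N from 120 to 208. If some participants consent and then miss their visit, the overlap falls slightly below 30 but does not vanish.

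The 22% excess in the SE, the type I error of about 1.6% and the fall in power from 69% to 52% are conditional on treating the overlapping groups as independent. In that case the error is conservative: it hides differences and does not create false positives.

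Severity is moderate. The primary outcomes are feasibility and acceptability, and the hypotheses in the Background concern those and the matched-cohort comparison. A reader might infer that the pilot's main conclusions are at risk; none of them rests on this contrast.

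**What to change.** In Quantitative data analysis, replace the first contrast with WNP research participants versus WNP patients who completed a visit and are not in the research program, adjusted for baseline weight. State that the comparison is non-randomised and exploratory because research participants self-select, and that adjustment for baseline weight does not remove that. Leave the comparison of all WNP patients with the matched cohort as planned.

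The cost is one phrase and one group indicator, with no new data. The comparator falls from about 150 to about 120 (150 − 30), and the SE of the full difference is 0.204 SD. The change should be made before the weight data are analysed, so that the redefinition does not look driven by results.

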### Study design

This is a clinical quality improvement project with an embedded single-arm pilot study. Specifically, patients with obesity who desire to lose weight will be referred by their PCP to the WNP. Patients scheduled for a WNP appointment will be offered the opportunity to participate in research; we will aim to recruit 30 participants to the research arm of the study Research activities include (1) surveys at 0, 6, and 12 months; (2) optional semi-structured interview participation at 0 and 6 months; and (3) use of a text messaging program for remote weight monitoring.

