### Pilot research program eligibility

Eligibility criteria included the following: (1) scheduled for a WNP; (2) willingness to complete surveys at 0, 6, and 12 months; (3) willingness and ability to self-report weight data by text message; and (4) willingness to receive outreach from the study team in response to text messaging data. Exclusion criteria are the inability to read or write English.

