**Figure 1. f1:**
[figure not shown]
Weight Navigation Program (WNP) design. Patients with obesity and ≥1 weight-related condition who desire to lose weight are referred by their primary care providers (PCPs) to the WNP. The Weight Navigator and patient develop a personalized obesity treatment plan using existing health system, community, and pharmacotherapeutic resources. The plan is communicated to PCPs via the Electronic Health Record (EHR). Patients self-report weight data using an EHR-based text messaging platform. The WNP team is notified of patients’ weight changes according to pre-specific thresholds. The WNP Care Manager initiates tailored outreach to support patients over time, address potential barriers, and facilitate changes to the treatment plan, if needed, to optimize patients’ outcomes.

Eligible patients who desire to lose weight may be referred to the WNP by their PCP. Referral orders will be reviewed by a clinical scheduler who will confirm patient eligibility, contact patients to schedule an appointment, and send patients a pre-visit weight history questionnaire via the patient Electronic Health Record (EHR) portal in advance of their appointment; weight history questionnaire topics are shown in Table 2. To ensure the Weight Navigator has access to relevant clinical data at the time of the WNP encounter, the referral order will prompt PCPs to obtain a comprehensive metabolic panel, complete blood count, hemoglobin HA1c, fasting glucose, fasting lipid panel, and thyroid function tests.

**Table 2. tbl2:** Weight history questionnaire topics

Birth history and birth weight Weight changes over time (eg, highest and lowest weights) Food frequency assessment (eg, frequency of eating fast food, processed food, high-fat food, sweets) Eating patterns and timing (eg, number of meals and snacks per day binge eating, night eating) Eating triggers Monthly food budget Prior weight loss successes and challenges Physical activity habits

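### Comparing the whole WNP group with its own research volunteers cannot show whether adding text-message weight monitoring works, even in a preliminary sense

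*Protocol article*

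**What the plan says.** The Study design section is open about the design: "This is a clinical quality improvement project with an embedded single-arm pilot study". Outcome measures lists, as part of its third category, "preliminary effectiveness of adding remote weight monitoring by text messaging to the WNP".

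Two places give a weight analysis relevant to that category:
- The change-in-weight entry under remote monitoring describes change from baseline to 12 months among text-messaging users only. It has no comparison group.
- Quantitative data analysis adds a between-group comparison, "all WNP participants versus WNP research participants", to be made "in weight using a difference-in-difference analytic approach".

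Entry to the monitored group is voluntary. Pilot research program eligibility requires agreement to three surveys, "willingness and ability to self-report weight data by text message; and (4) willingness to receive outreach from the study team", and excludes patients who cannot read or write English. Under Recruitment, those who wish to join consent online before the WNP visit, and enrolment stops at 30. The same section expects about 150 WNP patients in the first year.

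For the other contrast, with the neighbouring clinic, the article names matching on gender and approximate age. For the contrast at issue it names no step to make the groups alike. Limitations and opportunities does not mention self-selection into research.

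**The concern.** To learn what monitoring adds to the WNP, one must compare WNP patients with and without monitoring who would otherwise have had a similar weight course. The stated contrast departs from this in two ways.

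First, the groups are not separate: the research participants are part of the full WNP group they are compared with.

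Second, removing them from the comparator leaves unlike groups. Willingness to self-weigh, text a weight weekly and take calls is a form of engagement with weight control, and it plausibly goes with greater weight loss whether or not monitoring does anything. Difference-in-difference takes out fixed differences in starting weight and time trends common to both groups. It then assumes that, without monitoring, both groups would have changed in parallel. Selection on engagement threatens exactly that assumption.

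At stake is the pilot's statement about one of the three components of the WNP model named in the Discussion. Some or all of an apparent benefit of monitoring could be what volunteers would have achieved anyway.

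**Working it through.** The article gives no power, effect-size or SD figure for this contrast, so there is no stated result to reproduce. The check covers the structure of the contrast and then illustrates the bias.

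**Inputs from the article.** Research target 30; about 150 WNP patients in year 1 (both under Recruitment). Patients outside the research group: 150 − 30 = 120.

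**Step 1, overlap.** Let f = 30/150 = 0.20. Then

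mean(research) − mean(all WNP) = (1 − f) × [mean(research) − mean(non-research)] = 0.80 × the difference between separate groups.

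If the clinic sees 120 or 180 patients instead, the factor is 1 − 30/120 = 0.75 or 1 − 30/180 = 0.83.

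**Step 2, what overlap does to the test.** Assume an SD of weight change of 6 kg (8 kg in brackets).
- Separate groups, 30 v 120: SE = 6 × √(1/30 + 1/120) = 1.22 kg (1.63).
- Correct SE of the overlapping contrast: 0.80 × 1.22 = 0.98 kg (1.31).
- SE if the overlapping groups are wrongly treated as independent: 6 × √(1/30 + 1/150) = 1.20 kg (1.60).

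A nominal 5% test with the wrong SE needs a difference of 1.96 × 1.20/0.98 = 2.40 true SEs, which is a real level of about 1.6%. Correctly computed, overlap scales bias and SE alike, so removing it does not cure selection.

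**Step 3, illustrative selection bias.** The inputs here are assumptions, not from the article: motivated patients lose m = 2 to 4 kg more; they are 70 to 90% of volunteers and 40% of the others; monitoring has no effect.

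Spurious difference = m × (share motivated in research − share motivated outside).
- Low: 2 × (0.70 − 0.40) = 0.6 kg
- High: 4 × (0.90 − 0.40) = 2.0 kg
- As written, × 0.80: 0.48 to 1.6 kg, or about 0.5 to 1.6 kg

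These are about half to more than one and a half times the SE at an SD of 6 kg (0.6/1.22 = 0.5; 2.0/1.22 = 1.6).

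**Step 4, allowing for patients never invited.** Assume half of those invited consent. Then 60 are invited, 30 decline, and 90 of the 120 are never invited. Apply the 40% to decliners only, and let the never-invited resemble all invited patients.
- Volunteers 70% motivated: outside share = (30 × 0.40 + 90 × 0.55)/120 = 0.5125; gap 0.1875.
- Volunteers 90% motivated: outside share = (30 × 0.40 + 90 × 0.65)/120 = 0.5875; gap 0.3125.

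The spurious difference becomes 2 × 0.1875 = 0.4 kg to 4 × 0.3125 = 1.25 kg. It is smaller but not zero.

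**The case against.** The best reply is that this is a pilot whose primary outcomes are feasibility and acceptability. The hypotheses at the end of the Background concern those outcomes and the WNP against the matched cohort; none concerns monitoring. The weight outcome listed for monitoring is a within-group change, and the article never says that the contrast in Quantitative data analysis is meant to answer the monitoring question. This limits the consequences. It does not remove the point: the outcome category speaks of the effectiveness of adding monitoring, a within-group change cannot address adding, and no other contrast is offered.

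Three stronger readings are tempting and are not supported.

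- **That the comparator consists of decliners and ineligible patients.** As written it is every WNP patient, research participants included. Even with those removed, recruitment ends at 30, so many of the rest may simply never have been invited, which weakens the contrast in motivation.
- **That the analysis is unadjusted.** The article is a condensed account. Covariates may be in a fuller plan not shown, and difference-in-difference is itself a partial adjustment. What the article does fix is the pair of groups and the claim.
- **That treatment mix, for example more bariatric surgery among volunteers, drives the contrast.** Nothing in the article shows that treatment differs between the groups. The plan is also chosen at the visit, after research consent, so it is not a clean baseline confounder.

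**Conclusion.** The point holds. The stated contrast cannot isolate the effect of monitoring: the monitored group is self-selected on engagement, it is contained in its own comparator, and the method does not remove differences in weight course that follow from selection.

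Only the overlap can be sized from the article: a factor of about 0.8 at 30 of 150. The bias from selection cannot. The ranges of 0.6 to 2.0 kg (separate groups) and 0.5 to 1.6 kg (as written) rest wholly on the assumed motivation gap. The lower range of 0.4 to 1.25 kg further assumes 50% consent and never-invited patients who resemble the invited. They show that a null effect could look like a modest benefit; they do not show that it will.

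A reader might also infer that this contrast decides whether monitoring enters the later large trial. Future directions does not say so. It speaks of refining the programme from feasibility, acceptability, preliminary effectiveness and interview data together.

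**What to change.** In Quantitative data analysis:

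- Replace the comparator with WNP patients outside the research group, and use EHR clinic weights for both groups. Keep text-reported weights for the within-group description.
- Adjust for a small set of pre-consent variables already in the EHR: baseline BMI or weight, age, gender and, if feasible, visit date.
- Where numbers allow, show decliners and never-invited patients separately. The never-invited have not been selected by refusal and are the more informative comparison.
- Describe the initial treatment plan by group, or use it only in a sensitivity analysis.
- Restrict the comparator on English literacy only if that is recorded for non-research patients. Do not rely on the pre-visit questionnaire for adjustment without checking completion; the article says only that staff "send patients a pre-visit weight history questionnaire via the patient Electronic Health Record (EHR) portal in advance of their appointment".
- Report the result as a descriptive association, and word the third category in Outcome measures to match.

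In Limitations and opportunities, add self-selection into the monitored group.

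The cost is wording, EHR data that are largely being extracted already, and a log of who was invited and who declined. The downsides are a weaker claim about monitoring and room for only a few covariates with 30 monitored patients.
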